[14.2. Procedure to Cancel or Discontinue the Study 32](#_Toc4508514)

[14.3. Procedure for Cancelling or Discontinuing the Study at the Individual Institution 32](#_Toc4508515)

[14.4. Completion of the Study 32](#_Toc4508516)

[15. Data Management 33](#_Toc4508517)

[15.1. Data Entry Method and Management 33](#_Toc4508518)

[15.2. Identification of First-hand Entry into CRFs (Raw Data) 33](#_Toc4508519)

[16. Storing Raw Data and Other Records 33](#_Toc4508520)

[17. Direct Perusal of Raw Data 34](#_Toc4508521)

[18. Quality Control and Assurance in the Study 34](#_Toc4508522)

[18.1. Quality Control 34](#_Toc4508523)

[18.2. Quality Assurance 34](#_Toc4508524)

[19. Ethics 34](#_Toc4508525)

[20. Confidentiality 34](#_Toc4508526)

[21. Approved Clinical Study Review Board 3](#_Toc4508527)4

[22. Expected Advantages/Disadvantages Arising from the Study 3](#_Toc4508528)5

[22.1. Expected Advantages 3](#_Toc4508529)5

[22.2. Expected Disadvantages 35](#_Toc4508530)

[23. Compensation for Health Damage and Insurance 35](#_Toc4508531)

[23.1. Compensation for Health Damage 35](#_Toc4508532)

[23.2. Enrollment in Clinical Trial Insurance (Compensation Insurance) 35](#_Toc4508533)

[23.3. Enrollment in Liability Insurance 36](#_Toc4508534)

[24. Monetary Payments 36](#_Toc4508535)

[25. Conflicts of Interest and Research Funds 36](#_Toc4508536)

[26. Disclosure of Information regarding the Study 36](#_Toc4508537)

[27. Announcement of Results 36](#_Toc4508538)

[27.1. Annoucement Method 36](#_Toc4508539)

[27.2. Rules for Announcement 37](#_Toc4508540)

[28. Framework of Study 37](#_Toc4508541)

[29. References 38](#_Toc4508542)

1. **Study Outline**

| **Title** | **Phase II and phase III study regarding the Safety and Usefulness of a Nasal Pressure Monitor in Invasive Endoscopy Under Sedation** |
| --- | --- |
| **Objective** | To conduct a safety evaluation of a novel nasal pressure monitor used for patients who undergo invasive endoscopy (endoscopic retrograde cholangiopancreatography (ERCP), endoscopic submucosal dissection (ESD), endoscopic ultrasound guided fine needle aspiration (EUS-FNA), and oral double-balloon enteroscopy (DBE)), and evaluate its usefulness by means of a randomized single-blind controlled study to show its non-inferiority compared with capnography, which is the current standard of monitoring respiration. |

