This particular clinical study will be conducted to verify that there is no difference in the frequency of hypoxemia between the nasal pressure monitor group and the capnography group. SpO_2_<90% will be used as the general index for hypoxemia.

- 1. **Secondary Endpoints**

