**● Usefulness Evaluation (Phase III)**

The purpose of the usefulness evaluation is to prove that there is no difference in the incidence rate of hypoxemia (SpO2 <90%) between nasal pressure monitor group and capnography group, meaning that nasal pressure monitor is not inferior to capnography. According to reports, the incidence rate of declined SpO_2_ to under 90% in the endoscopic procedure under sedation is 12–47% when propofol is used as sedative,[4, 8, 9, 10] With regard to required number of registered patients, calculation based on 20% hypoxemia incidence rate, with non-inferiority margin of 15% for nasal pressure monitor against capnography, statistical power of 80% and significance level of 0.05 on both sides results in 224 patients for both groups (112 patients respectively).

- 1. **Handling Case Records**

In principle, the principal investigator and statistic specialists will decide on how the information on cases will be handled. In principle, the principal investigator and a statistic specialist will decide on how the information on cases will be handled.

- 1. **Handling Data**

When computing or analyzing data, as a rule, the data will be handled as shown below. If a question arises, it will be resolved through discussion between a statistic specialist and the study coordinator.

Missing data will not be supplemented. As sensitivity analysis, mixed-effects model for repeated measures, which compensates for data mission, will be used. Details will be contained in the Statistical Analysis Plan.

- 1. **Statistical Analysis Items and Plan**

● Safety Evaluation (Phase II)

Carry out analysis after the data is fixed following the completion of study involving all cases that are the subjects of safety evaluation. In the usefulness evaluation of all participants, the primary analysis will be the analysis of the FAS, and analysis of the PPS that complies with the Study Protocol will be carried out as a reference. Safety analysis will be carried out with the SAS.

Details of the statistical analysis will be determined in the Statistical Analysis Plan, which will be prepared elsewhere before the data is locked.

● Usefulness Evaluation (Phase III)

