Data from the usefulness evaluation will be analyzed after it is fixed following the completion of the study that involves all cases. In the usefulness evaluation of all participants, the primary analysis will be the analysis of the FAS, and analysis of the PPS that complies with the Study Protocol will be carried out as a reference. Safety analysis will be carried out with the SAS.

Details of the statistical analysis will be determined in the Statistical Analysis Plan, which will be prepared elsewhere before the data is locked.

- - 1. **Patient Background Analysis**

Patient data distribution and summary statistics will be obtained for each group by population. With regard to nominal variables, frequency of the category and proportion will be shown for each group. With regard to metric variables, summary statistics (number of cases, mean value, standard deviation, minimum value, median and maximum value) will be obtained for each group. In the comparison between two groups, Pearson's chi-square test will be used for nominal variables, but if the cells with expected frequency <5 account for 20% or more, Fisher’s exact test will be used. The t-test will be used for metric variables. Significance level will be 0.05 on both sides.

- - 1. **Usefulness Analysis**
       1. **Primary Analysis**

The main purpose of the study is to verify using the incidence rate of hypoxemia as primary endpoint that nasal pressure monitor is not inferior to capnography. Frequency and proportion in each group will be collated and **two-sided 95% confidence interval will be computed** When the upper limit of the 95% confidence interval in the comparison of hypoxemia incidence rate goes 15% lower than the non-inferiority margin, we deem that non-inferiority was proven.

To verify the null hypothesis that incidence rate of hypoxemia in both groups is the same in the primary analysis, Mantel–Haenszel test will be applied to the data stratified using assignment factors. Significance level will be 0.05 on both sides.

- - - 1. **Secondary Analysis**

Secondary analysis regarding usefulness will be carried out for the purpose of giving supplementary consideration to the results of primary analysis. No multiplicity adjustment will be carried out in the secondary endpoints analysis regarding usefulness .

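### The primary analysis in 11.5.2.1 puts a test of equal hypoxemia rates beside the non-inferiority confidence-interval rule without giving it a role, and equality is the only null hypothesis stated

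*Protocol*

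**What the plan says.** The Study Outline gives the Phase III objective as a randomized comparison "to show its non-inferiority compared with capnography, which is the current standard of monitoring respiration". Section 11.5.2.1 repeats this as the main purpose: to verify, using the "incidence rate of hypoxemia as primary endpoint that nasal pressure monitor is not inferior to capnography".

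Section 11.5.2.1 then contains two inferential statements.

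- First paragraph: a two-sided 95% confidence interval is computed, its upper limit is set against the 15% margin, and non-inferiority is deemed proven if the condition is met. The condition is worded so that the limit has to fall 15% below the margin, when presumably it should fall below a margin of 15%.
- Second paragraph: "To verify the null hypothesis that incidence rate of hypoxemia in both groups is the same in the primary analysis", a Mantel-Haenszel test stratified by the assignment factors is applied at two-sided 0.05. The text says nothing about what follows from its result or how it relates to the interval.

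Two other sections word the goal differently. Section 10.1, explaining the choice of primary endpoint, says the study is run to "verify that there is no difference in the frequency of hypoxemia between the nasal pressure monitor group and the capnography group", with no qualification. Section 11.2 says the purpose is to "prove that there is no difference in the incidence rate of hypoxemia (SpO2 <90%) between nasal pressure monitor group and capnography group", but the same sentence continues "meaning that nasal pressure monitor is not inferior to capnography".

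**The concern.** In a non-inferiority trial the null hypothesis is that the new monitor is worse by at least the margin. Equality of the two rates is the null of a superiority trial, and failing to reject it is not evidence that a 15-point excess has been excluded. The section nevertheless names equality as the null within the primary analysis and leaves the non-inferiority null to be inferred from the interval rule.

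This matters because the wording in 10.1 and 11.2 fits the wrong test. An author who reads that the aim was to show no difference, and who has a non-significant Mantel-Haenszel p-value from the primary analysis, could report the aim as met although the interval crosses 15 points. The device is unapproved and the endpoint is a safety event, so that misreport would run in the unfavourable direction. The garbled interval rule adds to the problem, because the equality test is the more clearly worded of the two.

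**Working it through.** **Inputs.** From 11.2: hypoxemia rate 20%, margin 15%, power 80%, two-sided 0.05 (one-sided 0.025), 112 per arm, literature range 12–47%. From 5.4.1: 1:1 allocation. Assumptions: the margin is an absolute difference, the interval is Wald, and the Mantel-Haenszel test is approximated by one stratum without continuity correction, because rates by stratum are not given.

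**Step 1. The sample size is a non-inferiority size.**
n per arm = 2 × 0.20 × 0.80 × (1.960 + 0.842)² / 0.15² = 111.6, so 112 per arm and 224 in total. This matches the protocol. Power at 112 is Φ(0.15 / √(0.32/112) − 1.960) = 80.1%.
A test of equality sized to detect 20% versus 35% would need [1.960 × √(2 × 0.275 × 0.725) + 0.842 × √(0.16 + 0.2275)]² / 0.15² = 137.9, so 138 per arm. The stated null is therefore not the hypothesis for which the trial is sized.

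**Step 2. How often the two criteria disagree.** All 113 × 113 outcomes for 112 per arm were enumerated with binomial probabilities. The interval rule is taken in its intended sense (upper limit below 15 points).

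| True rate, capnography / nasal pressure | Interval rule passes | Equality test non-significant | Non-significant and interval rule fails |
|---|---|---|---|
| 20% / 20% | 80.5% | 95.0% | 17.1% |
| 20% / 25% | 43.9% | 85.5% | 41.8% |
| 20% / 30% | 13.9% | 59.0% | 45.1% |
| 20% / 35% (on the margin) | 2.5% | 28.4% | 25.9% |
| 12% / 27% (on the margin) | 2.7% | 18.0% | 15.3% |
| 47% / 62% (on the margin) | 2.7% | 37.6% | 35.0% |

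At 20% versus 35% the ratio is 28.4 / 2.5, about 11. The 17.1% in the first row is not a false claim, since the rates there are equal; it mostly reflects the planned 80% power.

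**Step 3. One result that reads both ways.** Take 22/112 (19.6%) on capnography and 33/112 (29.5%) on nasal pressure.

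- Difference: 9.8 points.
- Unpooled standard error: √(0.196 × 0.804/112 + 0.295 × 0.705/112) = 0.057.
- 95% interval: 9.8 ± 1.96 × 5.7, that is −1.4 to 21.0 points. Non-inferiority fails.
- Equality test: p = 0.088, non-significant.

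**Step 4. The interval rule taken literally.** An upper limit 15 points below a 15-point margin means an upper limit below 0. At 20% in both arms this is met in 2.6% of trials, against the planned 80%. The literal text cannot be what is meant.

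**The case against.** The strongest reply is that a decision rule exists and is the right one. The paragraph just before the equality test ties proof of non-inferiority to the confidence limit and to nothing else. An interval that excludes 15 points is equivalent to rejecting a difference of 15 points or more, so the missing formal null is partly presentation. Section 11.2 explains its own phrase as "meaning that nasal pressure monitor is not inferior to capnography", and 10.1 gives reasons for choosing an endpoint, not a success criterion. An equality test beside a non-inferiority interval is not in itself an error, and its rank could be given in the statistical analysis plan.

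Most of this stands. A reader might infer that the protocol accepts a non-significant p-value as proof of non-inferiority, or that its false-claim rate is 28%. The documents support neither: no sentence attaches any consequence to the Mantel-Haenszel result, and the interval rule in its intended sense holds 2.5% at 20% versus 35%. The enumeration is also unstratified, whereas the plan stratifies by procedure (4), BMI (2) and sex (2), up to 4 × 2 × 2 = 16 strata, so the figures are approximate for the planned test.

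The reply does not remove the misstatement. The test is placed inside the primary analysis while secondary analyses have their own heading, equality is the only null written down, 10.1 carries no gloss, and the interval rule cannot be applied as worded. These are statements in the protocol, not details left open.

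**Conclusion.** The point holds as a misstatement with an avoidable risk of misreading, not as a wrong decision rule. Section 11.5.2.1 states a null hypothesis that does not fit the objective, the margin or the sample size, gives the test of it no role, and words the criterion that should decide so that its literal meaning is unusable.

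The size is conditional. Only if someone took the equality test as the decision would a monitor truly worse by 15 points pass in about 28% of trials at a 20% control rate (18% to 38% at control rates of 12% to 47%), against about 2.5% under the interval rule. These figures rest on 112 per arm, an absolute margin, a Wald interval and a single-stratum approximation.

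**What to change.** In 11.5.2.1:

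- State the null hypothesis as nasal pressure rate minus capnography rate of 15 percentage points or more, rejected only when the upper limit of the two-sided 95% confidence interval of that difference is below 15 percentage points. This also replaces the garbled sentence.
- Name this as the sole primary criterion.
- Label the Mantel-Haenszel equality test either as supportive or as a superiority step run only after non-inferiority has been shown, and say that a non-significant result supports no claim.

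In 10.1 and 11.2, replace the no-difference wording with non-inferior, meaning not worse by 15 percentage points or more.

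The cost is a few sentences in a protocol amendment. Section 11 already requires a protocol revision when the primary analysis method changes, so the protocol is the place for it. The 224 patients and the data collected stay as they are.

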b: During treatment the screens will be monitored and the state of respiration when SpO2 drops below 90% (frequency) and 95% (frequency) and oxygen desaturation (<90% and <95%) occurs will be recorded. In addition to the above, assistant investigators will analyze monitor records after the completion of the monitoring period and record the state of respiration when SpO_2_ drops below 90% (frequency and duration) and 95% (frequency), when oxygen saturation (<90% and <95%) occurs, and the frequency with which the patient experiences apnea (≥20 sec). Analysis of monitor records will be carried out for three hours after the completion of treatment for the Safety Evaluation (Phase II), and for one hour after the completion of the treatment for the Usefulness Evaluation (Phase III). (In the Safety Evaluation (Phase II), if respiratory abnormalities occur frequently after one hour has passed following the completion of the treatment, the duration of the observation period after the completion of the treatment for the usefulness evaluation will be reconsidered.)

c: In the post-treatment monitor analysis by the assistant investigators, if oxygen desaturation was not observed even without respiratory waveforms of more than three minutes, this will still be deemed to be a false alarm.

d: If technical trouble occurs, such as apnea or a respiratory abnormality being displayed due to a dislodged sensor, or if bodily movement occurs that requires two or more people to secure the safety of the patient or to continue the procedure, the doctor in charge of sedation will record such matters.

e: Operators will evaluate coordination during the treatment using VAS after the treatment has been completed. After confirming that the patient is fully awake after the treatment, on the same day, the degree of patient satisfaction regarding the treatment will be evaluated using VAS.

f: All events that occurred from the time of the commencement of the treatment will be checked to see if they equate to adverse events. All adverse events that occurred during the treatment period will be followed up during the post-treatment observation period. For details please see “8. Handling Adverse Events.”

g: If the study is discontinued, data that was scheduled to be obtained on the day following treatment will be collected, and no data will be collected after that using the testing equipment.

- - 1. Screening

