**Secondary Endpoints for Usefulness**

- Frequency of apnea (≥20 seconds)
- Degree of participant satisfaction (VAS)
- Coordination during procedure (VAS)

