Frequency of apnea (≥20 sec), degree of patients’ satisfaction and coordination during procedure will be evaluated with capnography group and nasal pressure monitor group, and the difference between those two groups will be analyzed using Pearson’s chi-square test. Significance level will be 0.05 on both sides, and confidence interval, and **two-sided 95% confidence interval will be computed.**

- - 1. **Safety Analysis**

Frequency of adverse event occurrence is the evaluation items to consider safety, therefore data table will be created. To estimate the proportion, exact 95% confidence interval for binomial distribution will computed for each group. Inter-group comparison will be carried out as required using Fisher's exact test.

- - 1. **Intermediate Analysis**

Data will be locked when registration of all cases for the Safety Evaluation (Phase II) is completed. The fixed analysis results will be disclosed to the independent data-monitoring committee (IDMC) (see 11.6) that oversees the study. The IDMC will evaluate the fixed data, and when they find the following situation, the study will be discontinued without carrying out registration for the usefulness evaluation.

- Rate of discontinued cases due to default accounted for 20% or more.
- Hypoxemia (SpO_2_<90%) was found in 60% or more of the cases.
- The IDMC determined that it will be inappropriate to conduct usefulness evaluation.

When the IDMC verified the safety, the participants will be registered for the usefulness evaluation. No intermediate analysis will be carried out in the usefulness evaluation.

- 1. **Independent Data-Monitoring Committee (IDMC)**

The independent data-monitoring committee (IDMC) will be established for this study. The IDMC will be independent of the people who conduct the study, and consist of two or more specialists whose position have no conflict of interest with this particular clinical study. The IDMC will provide appropriate advice and guidance in order to secure the safety of the participants and ethical and scientific soundness, based on the data monitoring protocol that is determined elsewhere for the purpose of securing safety of the participants. In cases where serious adverse events appear in this clinical study, the principal investigator may request the IDMC to deliberate concerning whether or not the study should be continued or revision of the Study Protocol. The IDMC will serve in writing the results of the deliberation to the principal investigator.

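### The protocol fixes Pearson's chi-square for two VAS endpoints, where it is a poor test, and leaves the unit of the apnea endpoint unclear

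*Protocol*

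**What the plan says.** Protocol section 11.5.2.2 (Secondary Analysis) takes three endpoints together: "Frequency of apnea (≥20 sec), degree of patients’ satisfaction and coordination during procedure will be evaluated" in both groups, and "the difference between those two groups will be analyzed using Pearson’s chi-square test", at a two-sided 0.05 level. It also promises a two-sided 95% confidence interval but does not say for which quantity.

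Two of the three endpoints are VAS scores. Section 10.2 lists them as such, and footnote e to the schedule in section 7.1 says how they are obtained: "Operators will evaluate coordination during the treatment using VAS after the treatment has been completed", and for the patient, "the degree of patient satisfaction regarding the treatment will be evaluated using VAS". The protocol gives no categories or cut-off for either.

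For patient background (section 11.5.1) the protocol matches test to data type. Chi-square is for nominal variables, with Fisher's exact test when cells are sparse, and "The t-test will be used for metric variables". Section 11.5.2.2 repeats neither the distinction nor the sparse-cell rule.

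For apnea, footnote b to the same schedule has the assistant investigators record "the frequency with which the patient experiences apnea (≥20 sec"), which is a count per patient. Section 11.5.3, however, treats adverse-event frequency as a share of patients: "To estimate the proportion, exact 95% confidence interval for binomial distribution". Section 10.1 likewise speaks of the frequency of hypoxemia for an endpoint defined as cases over participants.

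**The concern.** Pearson's chi-square compares how patients fall into unordered categories. Applied to a VAS as it stands, it treats every distinct score as its own category, so nearly all cells are sparse and the ordering of the scores is lost. To make it workable someone must first group the scores, which discards information. In neither case does the test yield an effect estimate to which the promised confidence interval could belong.

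The direction of the error matters here. The trial aims to show that the two monitors perform alike, and section 11.5.2.1 is followed by secondary analyses meant to shed further light on that result. A test with little power will usually return p > 0.05 even when satisfaction or coordination truly differs, and that could be read as agreement.

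For apnea, the data collected and the test named fit together only under one of two readings, and the protocol does not say which is meant.

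**Working it through.** **Inputs from the protocol.** 224 patients, 112 per group; hypoxemia rate 20%; margin 15 percentage points; 80% power; two-sided 0.05 (section 11.2). Test as in section 11.5.2.2.

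**Assumed, because the protocol gives none.** VAS SD 20 mm, means 50 or 70 mm, true difference 0.374 SD (7.5 mm) or 0.40 SD (8 mm). Apnea counts negative binomial with mean 1 or 2 per patient.

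**Step 1: the plan's own sample size.** n = (1.960 + 0.842)² × 2 × 0.20 × 0.80 / 0.15² = 7.849 × 0.32 / 0.0225 = 111.6, so 112 per arm and 224 in total. This matches.

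**Step 2: what a t-test can detect at 112 per arm.** For 80% power, d = (1.960 + 0.842) × √(2/112) = 2.802 × 0.1336 = 0.374 SD. At d = 0.40, power = Φ(0.40 × √56 − 1.960) = Φ(1.033) = 85%.

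**Step 3: chi-square after a median split.** The shares above the pooled median are Φ(d/2) and Φ(−d/2).
- d = 0.374: 57.4% v 42.6%, difference 0.1485; SE 0.0668 under the null and 0.0661 under the alternative. Power = Φ((0.1485 − 1.960 × 0.0668)/0.0661) = 60%.
- d = 0.40: 57.9% v 42.1%; the same formula gives 66%.
- Reaching 80% at d = 0.374 would take 177 per arm.

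**Step 4: simulation of all the options.** Normal scores, rounded to 1 mm and clipped to 0–100, 112 per arm, 2,000 to 3,000 trials per setting. The ranges cover both means and repeated runs.

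| Test | Rejects when there is no difference | Power at 0.374 SD | Power at 0.40 SD |
|---|---|---|---|
| t-test | 4–5% | 78–81% | 82–86% |
| Wilcoxon | 4–5% | 77–79% | 82–85% |
| Chi-square, median split | 5–6% | 61–62% | 66–67% |
| Chi-square, 10-mm classes | 3–5% | 37–39% | 43–47% |
| Chi-square, raw scores | about 1% | 3–6% | 3–7% |

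On raw scores 98% or more of the cells have an expected count below 5. Even at 0.5 SD, raw-score chi-square has only 7–14% power, against about 96% for the t-test.

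**Step 5: apnea under each reading.** The type I error at a nominal 5% (simulated, dispersion k = 0.5 to 1) is:
- any episode, yes/no per patient: 4–5%, so the test is valid;
- patients grouped by their number of episodes: 1.8–2.5%, so it is conservative;
- episodes pooled as if independent: 16–30%. As a check, with mean 1 and k = 1 the variance is 1 + 1/1 = 2, and P(|Z| > 1.960/√2) = P(|Z| > 1.386) = 16.6%.

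With assumed means of 1 v 1.6, power is 26–42% for yes/no, 11–26% for grouped counts and 40–64% for a rank test on the counts.

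**The case against.** A reader might infer that chi-square is invalid for all three endpoints and that the apnea comparison has an inflated error rate. The documents do not support that. Sections 10.1 and 11.5.3 use frequency for a share of patients, so a yes/no reading of apnea is open; it needs no cut-off beyond the stated 20 seconds, and chi-square then holds its level. The inflation in step 5 requires episodes as the unit of analysis, which the protocol never states. What remains for apnea is an undefined unit.

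For the VAS endpoints, a grouped score would give a valid test that is merely less efficient, and the lowest power figures apply only if raw scores are cross-tabulated. On raw scores the test is conservative, so it would not produce false claims of a difference. This stands, and it is why the loss is given as a range.

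Section 11 leaves details to an SAP that is not shown and may supply categories. The absence of a cut-off is therefore not itself a fault, and it would be speculation to say that one would be chosen after the fact. But the protocol names the test, and even with categories it remains a weak choice for a metric score.

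Nor does the t-test rule in section 11.5.1 contradict section 11.5.2.2 outright: it governs background variables. It shows only that the protocol treats metric data differently elsewhere.

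Finally, the endpoints are supplementary, carry no multiplicity adjustment and did not drive the sample size. This also stands and limits the weight of the point.

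**Conclusion.** The point holds for satisfaction and coordination: the named test does not suit a VAS. At 112 per arm, and a true difference for which a t-test has about 78–86% power, chi-square has about 3–7% on raw scores, 37–47% on 10-mm classes and 60–67% after a median split. These figures rest on an assumed SD of 20 mm, roughly normal scores and a difference of 0.37 to 0.40 SD. The ranking of the tests was the same in every setting examined.

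For apnea the conclusion is narrower: the protocol must say whether the endpoint is yes/no or a count per patient. The non-inferiority analysis of hypoxemia is untouched. This should be corrected, but it does not threaten the trial's main conclusion.

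**What to change.** In section 11.5.2.2, and in the SAP to match:

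- **Satisfaction and coordination:** replace chi-square by the difference in mean VAS with a two-sided 95% CI, from a t-test or a linear model with the assignment factors. If the scores are skewed, use a Wilcoxon test. State that a non-significant result is not evidence of similarity.
- **Apnea:** choose one definition. Either any apnea of at least 20 seconds, yes/no per patient, keeping chi-square and reporting the risk difference with 95% CI; or the number of episodes per patient, compared by a rank test or a negative binomial rate ratio with 95% CI. Do not analyze episodes as independent units.

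The cost is a wording change before the data are seen. No extra patients, visits or measurements are needed. Under section 11 only a change to the primary endpoint's definition or analysis obliges a protocol revision, so the SAP could carry this alone, but correcting both keeps them consistent.
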